**Figure 1 figure1:**
[figure not shown]
Study flowchart illustrating the trial design, including the screening of 126 eligible participants with cerebral infarction in the recovery phase, randomization into 2 groups (Qizhi Jieyu pill plus conventional treatment versus conventional treatment alone), a 12-week treatment period, and follow-up assessments at weeks 12, 24, 36, and 48. The outcomes assessed include changes in National Institutes of Health Stroke Scale (NIHSS) scores, traditional Chinese medicine (TCM) symptom scores, recurrence rates, Rankin Scale scores, and adverse events.

### Participants

#### Cerebral Infarction Diagnostic Criteria

Referring to the 2014 Chinese guidelines for diagnosis and treatment of acute cerebral infarction issued by the Cerebrovascular Disease Group of the Neurology Branch of the Chinese Medical Association [17], diagnostic criteria include sudden onset, focal neurological deficits (occasionally generalized), symptoms and signs lasting more than 24 hours, exclusion of nonvascular brain lesions, and computed tomography (CT) or magnetic resonance imagining (MRI) excluding cerebral hemorrhage or other abnormalities, with a responsible ischemic lesion.

#### Diagnostic Criteria for the Recovery Phase of Cerebral Infarction

Referring to the 2017 guidelines for integrated traditional Chinese and western medicine diagnosis and treatment of cerebral infarction in China [18], within 6 hours of onset is the hyperacute phase, around 2 weeks postonset is the acute phase, 2 weeks to 6 months postonset is the recovery period, and more than 6 months postonset is the sequelae phase.

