#### Inclusion Criteria

Criteria for inclusion in the study are as follows:

Patients diagnosed with cerebral infarction and currently in the recovery phase.Patients aged 30-70 years.Patients who voluntarily signed the informed consent form.

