### Outcomes

#### Primary Outcome

The primary outcome is the change in NIHSS score at 48 weeks [21]. This scale evaluates levels of consciousness, command compliance, eye movement, visual field defects, facial paralysis, limb motor dysfunction, ataxia, speech expression, and other parameters.

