### Randomization

Random numbers will be generated using SAS statistical software (version 9.4), and participants will be assigned to the intervention and control groups in a 1:1 ratio. After screening and informed consent, patients will be randomly assigned to one of the two groups based on their order of enrolment. The drug number for each participant will remain unchanged throughout the study. In the case of a clinical emergency, the participant’s random code and group assignment may be unblinded.

Due to the nature of the intervention, participant and clinician blinding is not feasible. However, outcome assessors will be blinded to group assignments to minimize detection bias, especially for subjective measures such as TCM symptom scores.

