#### Statistical Analysis Plan

A statistical analysis plan was formulated prior to the start of the study. It will be finalized after discussion among the statisticians, principal investigators, and sponsor before database lock. This plan describes only the standard statistical requirements.

Statistical analysis will be conducted using SAS version 9.4. All hypothesis tests will be 2-sided, with a significance level of α=.05. *P* values less than or equal to .05 will be considered statistically significant.

For continuous variables, mean, SD, minimum, maximum, and median values will be used for descriptive statistics. Independent samples *t* tests (for normally distributed data) or Wilcoxon rank-sum tests (for non-normally distributed data) will be used for hypothesis testing. Normality of continuous variables will be assessed using the Shapiro-Wilk test before choosing appropriate parametric or nonparametric tests.

For categorical variables, frequency and percentages will be used for description. Chi-square tests or Fisher exact tests will be used for hypothesis testing. Ordinal variables will be analyzed using the Wilcoxon rank-sum test.

Logistic regression will be used to control for confounding factors affecting the outcome measures. We will also analyze the association between syndrome evolution patterns and therapeutic efficacy. In parallel, multivariate linear regression will be used to explore the relationship between outcomes and potential confounders, such as baseline NIHSS score, study center, age, and sex. For adverse events potentially associated with animal-derived components—including itching, rash, allergic reactions, and gastrointestinal discomfort—we will conduct attribution analysis and report their incidence separately.

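### The stated test of week-48 NIHSS change is unadjusted although entry spans 2 weeks to 6 months after onset, so variation explained by onset time and baseline NIHSS stays in its error term: a loss of precision, not a bias

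*Protocol article*

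**What the plan says.** All references are to the protocol article.

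- **Entry window.** Diagnostic Criteria for the Recovery Phase of Cerebral Infarction: "2 weeks to 6 months postonset is the recovery period". Inclusion Criteria admits "Patients diagnosed with cerebral infarction and currently in the recovery phase" and sets no tighter limit on time since onset.
- **Primary outcome.** Primary Outcome: "The primary outcome is the change in NIHSS score at 48 weeks".
- **Between-group test.** For continuous variables, Statistical Analysis Plan gives an independent-samples t test for normal data, "or Wilcoxon rank-sum tests (for non-normally distributed data) will be used for hypothesis testing". No covariate enters either test, and no separate test is given for the primary outcome.
- **Covariates.** The same section adds a linear regression, run alongside those tests and "used to explore the relationship between outcomes and potential confounders, such as baseline NIHSS score, study center, age, and sex". It also says that "Logistic regression will be used to control for confounding factors affecting the outcome measures", naming no factors. Time since onset is not named in either place.
- **Allocation.** Randomization: "participants will be assigned to the intervention and control groups in a 1:1 ratio". Stratification by time since onset is not mentioned.
- **Timing.** Sample Size Calculation plans a midterm reassessment that uses the observed effect size. Statistical Analysis Plan says the plan is finalised before database lock.

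**The concern.** The window runs from about 14 to about 182 days after onset, a 13-fold range. The article divides the disease course by time since onset alone and places the sequelae phase after 6 months. A patient who enters at 2 weeks spends about 24 of the 48 follow-up weeks inside the article's own recovery period (26 − 2 = 24). A patient who enters at 6 months spends essentially all 48 weeks in the sequelae phase. The same baseline NIHSS score could then leave different room for change in these two patients.

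If so, part of the spread in 48-week change is predictable at baseline, and an unadjusted test counts it as noise. The confidence interval for the primary comparison is then wider than it needs to be, and a chance difference between arms in onset time is not allowed for in the estimate. The same holds for baseline NIHSS and centre. The article names both as potential confounders but keeps them out of the stated test.

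**Working it through.** **Inputs**

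- SD 2.0, two-sided α 0.05, β 0.2, 52 per group before dropout, 63 per group recruited, 20% dropout (Sample Size Calculation; sidedness from Statistical Analysis Plan).
- Changes of about 4.9 (control) and about 6 (study group), a difference of 6 − 4.9 = 1.1 (Sample Size Calculation). That section also states a difference of 2; the next step shows which one gives 52.
- Partial correlation r of onset time with week-48 NIHSS change, given baseline NIHSS and centre: **not in the article, so an assumption**, shown from 0 to 0.5.

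**1. Reproduce the plan's figure**

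n per group = 2 (1.960 + 0.842)² σ² / δ²

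- δ = 1.1, σ = 2.0: 2 × 7.849 × 4 / 1.21 = 51.9, rounded up to 52. This matches.
- δ = 2, σ = 2.0: 2 × 7.849 × 4 / 4 = 15.7, rounded up to 16. This does not match.

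The working therefore uses 1.1. At that difference and 52 per group, power is 80.1% by the normal approximation and 79.3% by the two-sample t test. The t-test values are used below.

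**2. What adjustment changes**

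A covariate with partial correlation r reduces the residual SD from σ to σ√(1 − r²). The equivalent gain in sample size is 1/(1 − r²). Here σ stands for the residual SD before onset time is added, kept at 2.0 because the article gives no other figure.

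| r (assumed) | Residual SD | Variance removed | Worth in patients | Power, 52 per arm |
|---|---|---|---|---|
| 0 | 2.000 | 0% | 0% | 79.3% |
| 0.2 | 1.960 | 4% | about 4% more | 80.9% |
| 0.3 | 1.908 | 9% | about 10% more | 82.9% |
| 0.5 | 1.732 | 25% | about 33% more | 89.4% |

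Taking 20% off 63 leaves about 50 per arm. Power there is 77.7% unadjusted and 81.4% at r = 0.3.

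**3. The cost of the extra term**

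With 104 patients analysed, the two-group comparison has 102 residual degrees of freedom. Onset time takes one, leaving 101, and every power in the table moves by about 0.01 percentage points or less. If r is 0, practically nothing is lost.

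**4. Which analysis is affected**

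The four named variables belong to the exploratory regression. Adding onset time to that list would leave the t or Wilcoxon test as it is. The precision is recovered only if the primary comparison itself is made from the adjusted model.

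**The case against.** The strongest case against raising this has four parts.

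- **The list is open and the plan is not final.** It is introduced as examples, and a full covariate list is commonly left to the statistical analysis plan. This stands: a reader might infer that the plan has excluded time since onset, and the article does not say so. The point here is narrower. The test that the article does state for a continuous outcome has no covariates.
- **Onset time's absence from the list is not the cause.** This also stands. Baseline NIHSS, centre, age and sex are equally outside the stated test, so the cause is the unadjusted primary comparison.
- **Its prognostic strength is not documented.** A reader might call onset time a known or strong predictor. The article calls the recovery phase crucial and describes stroke recovery as progressive, but it gives no figure linking onset time to 48-week NIHSS change. Baseline NIHSS may carry part of the same information, which is why r must be a partial correlation. It could be small: at 0.2 the gain is 1.6 percentage points.
- **The unadjusted test is valid.** A reader might infer that chance imbalance in onset time makes the comparison biased. It does not. Randomisation keeps the comparison unbiased in expectation, and the test's type I error rate already allows for such imbalance.

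What remains is that a better primary analysis is available at almost no cost, and that the open list is best fixed before comparative results are seen.

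**Conclusion.** The point holds as one of precision and prespecification. As written, the comparison of week-48 NIHSS change leaves in its error term whatever baseline NIHSS, centre and onset time explain, in a population whose onset time varies about 13-fold.

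For onset time alone, the gain in power at 52 per arm runs from nothing (r = 0) through 1.6 points (r = 0.2) and 3.6 points (r = 0.3) to 10.1 points (r = 0.5). These figures rest on the difference of 1.1 and SD of 2.0 that reproduce the plan's 52, on a linear relation with the outcome, and on an r that the article does not supply. The gain from baseline NIHSS and centre is not quantified here, because the article gives no correlation for those either.

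The article does not support reading this as a biased comparison, an invalid test, or a decision to leave onset time out.

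**What to change.** Before the midterm look, prespecify a linear model as the primary analysis of week-48 NIHSS change, with treatment, baseline NIHSS, centre and time from onset to randomisation as fixed covariates. State the form in which onset time enters (for example, continuous on the log-days scale). Take the treatment estimate and confidence interval from this model, in place of the choice between t and Wilcoxon tests for the primary outcome. The unadjusted comparison can be kept as supportive. Report time since onset by arm in the baseline table.

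The cost is wording in the analysis plan and one degree of freedom for onset time. Onset timing already has to be established to confirm that a patient is in the recovery phase. The only data step is to make sure that the date itself is recorded on the case report form.

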#### Diagnostic Criteria for Phlegm-Stasis Obstruction Syndrome

The diagnostic criteria are based on the Standards for the TCM Diagnosis and Therapeutic Evaluation of Stroke (Trial Version, 1995), drafted by the Encephalopathy Emergency Research Collaboration Group of the State Administration of Traditional Chinese Medicine [19], and include dizziness and vertigo, profuse and sticky phlegm, dark tongue body, thin white or greasy white tongue coating, and a wiry-slippery pulse.

#### Inclusion Criteria

Criteria for inclusion in the study are as follows:

Patients diagnosed with cerebral infarction and currently in the recovery phase.Patients aged 30-70 years.Patients who voluntarily signed the informed consent form.

#### Exclusion Criteria

Criteria for exclusion from the study include the following:

Patients diagnosed with intracranial hemorrhagic disease by head CT or MRI.Patients with abnormal clinical laboratory tests, including alanine aminotransferase or aspartate aminotransferase ≥2.5 times the upper limit of normal or creatinine above the upper limit of normal.Patients unable to understand or comply with the study protocol due to severe psychiatric, cognitive, or emotional disorders.Patients with other diseases affecting limb mobility that may impact neurological assessments.Women who are pregnant, breastfeeding, or planning to conceive in the near future.Patients with a suspected or confirmed history of alcohol or drug abuse within 6 months prior to onset.Patients with a known or suspected allergy to the investigational drug or those with an allergic constitution.Patients who have participated in another clinical trial within the last 3 months.Other situations judged by the investigator to reduce the likelihood of enrolment or complicate enrolment.

#### Criteria for Case Elimination

The following are criteria for case elimination:

After enrollment, cases were found not to meet the inclusion criteria or to meet the exclusion criteria.Cases involving the use of prohibited medications as per protocol, necessitating elimination due to protocol violations.Cases in which the medication was never received or the exposure did not meet the experimental requirements.Cases with no evaluable records after medication administration.

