#### Safety Outcomes

Safety will be assessed using the following monitoring indicators:

Vital signs, including temperature, blood pressure, respiration rate, and heart rate, checked every 12 weeks.Routine tests, including blood, urine, and stool tests, every 12 weeks.Other labs and diagnostics, including electrocardiograms, liver function tests (alanine aminotransferase, aspartate aminotransferase, gamma-glutamyltransferase, alkaline phosphatase, and total bilirubin), and kidney function tests (blood urea nitrogen and creatine), every 12 weeks.Adverse events: From the time the participant enters the study until the final follow-up, adverse events will be monitored for 48 weeks. All information related to adverse events will be carefully recorded at all times. Serious adverse events refer to any unexpected clinical events occurring at any dose that result in hospitalization, prolongation of existing hospitalization, disability, impaired ability to work, life-threatening conditions or death, or congenital malformations. Serious adverse events will be reported to the study center and the principal medical ethics committee. In addition, they will be reported to the National Medical Products Administration within 24 hours. Meanwhile, we will specifically record adverse events potentially related to animal-derived components, such as itching, rash, allergic reactions, and gastrointestinal discomfort.

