### Statistical Analysis

#### Definition and Selection of Statistical Analysis Datasets

Participants will be categorized into the following analysis sets:

Full analysis set: This includes all randomized participants who have at least 1 postbaseline efficacy evaluation. This is the main dataset for efficacy analysis. Missing values for primary efficacy outcomes will be imputed using the last observation carried forward method. Missing values for secondary efficacy and safety outcomes will not be imputed. For secondary efficacy endpoints and safety data, descriptive analysis and complete-case analysis will be conducted based on actual observed values. Although last observation carried forward is commonly used in clinical trials, we acknowledge its limitations in progressive conditions such as stroke recovery. We will perform sensitivity analyses using multiple imputation methods to evaluate the robustness of our results.Per protocol set: This includes all participants in the full analysis set who meet inclusion criteria, do not meet exclusion criteria, complete the treatment, and do not have major protocol deviations. This is the secondary dataset for efficacy evaluation.Safety set: This includes all randomized participants who received at least 1 dose of Qizhi Jieyu pill and had at least 1 postbaseline safety evaluation.

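### The safety set can omit pill recipients who leave before week 12, and the case-elimination rule names no analysis set and overlaps with the withdrawal rule

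*Protocol article*

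**What the plan says.** Four parts of the protocol article bear on who is counted for safety.

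- **Definition and Selection of Statistical Analysis Datasets.** The safety set is the randomised participants who took the pill at least once "and had at least 1 postbaseline safety evaluation". It has no eligibility condition, and neither does the full analysis set. Only the per protocol set requires the entry criteria to be satisfied.
- **Criteria for Case Elimination.** The list starts with "After enrollment, cases were found not to meet the inclusion criteria or to meet the exclusion criteria" and ends with "Cases with no evaluable records after medication administration". Between these it names prohibited medication, medication never received and insufficient exposure. It does not say from which dataset a case is eliminated, or what happens to the data.
- **Conditions and Procedures for Participant Withdrawal.** Complications arising on study, poor compliance (outside 80% to 120% of prescribed medication), prohibited medication and intolerable reactions lead to withdrawal. Case report forms are kept, and adverse events are analysed in what the section calls the full dataset.
- **Safety Outcomes and Table 1.** "From the time the participant enters the study until the final follow-up, adverse events will be monitored for 48 weeks". The first scheduled visit after baseline is week 12, within 7 days either way.

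**The concern.** A safety population should not depend on whether a treated person came back to be assessed, because failing to come back may be a consequence of the harm. Here the first scheduled assessment falls at the end of exposure, so the condition covers almost the whole treatment period. Participants who stop early because of a reaction are the ones most likely to fail it, and losing them would make the pill look safer.

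The elimination list adds uncertainty. Three of the nine exclusion criteria coincide with findings that are checked or recorded during the study: "alanine aminotransferase or aspartate aminotransferase ≥2.5 times the upper limit of normal or creatinine above the upper limit of normal"; "Patients diagnosed with intracranial hemorrhagic disease by head CT or MRI"; and "Patients with a known or suspected allergy to the investigational drug or those with an allergic constitution". A site could misapply the first elimination criterion to an abnormality that appears after randomisation. According to the Randomization section, clinicians know the allocation, so any discretion over who is eliminated is exercised with that knowledge.

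**Working it through.** **1. When can a pill recipient first satisfy the safety-set condition through a scheduled visit?**
- Treatment lasts 12 weeks (Intervention).
- The first scheduled postbaseline safety assessment is at 12 weeks ± 7 days (Table 1), so week 11 at the earliest.
- No scheduled safety assessment falls between the first dose and week 11. A participant who leaves in that interval meets the condition only if an unscheduled report counts as an evaluation, and the article does not say whether it does.

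**2. Does the withdrawal section rescue these participants?** Its reference to the full dataset can be read in two ways.
- If it means the full analysis set, entry needs an efficacy evaluation after baseline. Table 1 also schedules that first at week 12, so the same people are missing.
- If it means everyone, it conflicts with the safety-set definition.

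Either way the two sections need reconciling.

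**3. How many could be affected?**
- Inputs from Sample Size Calculation: 63 per group, 20% dropout. The plan's 63 is reproduced as 52 × 1.20 = 62.4, rounded up.
- Assumption: the 20% applies equally to both arms.
- Upper end, all pill-arm dropout before the first visit: 0.20 × 63 = 12.6, about 13 participants.
- Lower end, all dropout after the first visit: 0.
- One lost participant is 1/63 = 1.6% of the arm.

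The article gives no dropout timing, so the range cannot be narrowed. It counts participants who could lack a scheduled evaluation. It does not count harms.

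**4. Elimination and withdrawal side by side.**

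| Situation | Case elimination | Withdrawal |
|---|---|---|
| Prohibited medication | Eliminated, dataset not named | Withdrawn, data kept and analysed |
| Inadequate exposure | Eliminated, dataset not named | Withdrawn as poor compliance if under 80%, data kept and analysed |
| Complication arising on study | Not named | Withdrawn, data kept and analysed |

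For the first two rows nothing decides which rule applies.

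**5. Is elimination plainly confined to the per protocol set?** The text does not say so. Two items on the list, medication never received and no evaluable records, mirror the entry conditions of the safety set and the full analysis set. The per protocol set is already a subset of the full analysis set, so the no-records item would add little if the list served only to define the per protocol set.

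**6. Does the first criterion refer to status during follow-up?** Inclusion requires the recovery phase, defined as 2 weeks to 6 months after onset. Someone enrolled at the earliest point, 2 weeks, is at least 2 + 48 = 50 weeks from onset at the final visit, allowing nothing for the visit window. Judged on follow-up status, everyone who reached that visit would be eliminated. Table 1 also marks the eligibility check at screening and baseline only. The coherent reading is a patient wrongly enrolled and discovered later.

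**The case against.** A reader might infer something stronger: that the exclusion criteria are the toxicities being monitored, so that a raised liver enzyme, a bleed or an allergic reaction on study removes the participant and the harm from the data. The documents do not support this.

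- Only three of the nine criteria overlap with on-study findings.
- The follow-up reading would eliminate every completer, as shown above.
- Complications arising on study have their own route, withdrawal, with adverse events still analysed.
- No sentence links elimination to the safety set, which has no eligibility condition. A participant with an abnormal liver test at week 12 has, by that test, had a safety evaluation and qualifies.

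This defence stands and reduces the first elimination criterion to a matter of wording.

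On the safety set, the defence is that the condition speaks of an evaluation, not a scheduled visit. Adverse events are to be recorded throughout, and serious ones reported to the regulator within 24 hours, so an early reaction or death that is reported could reasonably count. That is a fair reading, but the article does not state it. It also does not help a participant who stops attending without reporting anything, which the withdrawal section expressly foresees. This part of the concern remains.

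**Conclusion.** The point holds as two wording defects of unequal weight.

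The firmer one is the safety-set condition. As written, it can drop a treated participant who leaves before about week 11, including someone who leaves because of a reaction. The exposure is 0 to about 13 of 63 pill participants, assuming 20% dropout in each arm and unknown timing. If such an exclusion is related to harm, it favours the pill, but the article gives no basis for estimating a bias in any event rate.

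The second is an ambiguity. Case elimination names no dataset, overlaps with a withdrawal rule that keeps the data, and could be misapplied to three kinds of on-study finding. It does not establish that harms will be removed. A separately held analysis plan may settle both matters, but the definitions printed here do not.

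**What to change.** - In the analysis-dataset section, delete the requirement for a safety evaluation after baseline, so that every treated participant is in the safety set and any event, death or contact after the start of treatment counts.
- In Criteria for Case Elimination, state that the first item concerns eligibility status at randomisation, that elimination removes a case from the per protocol set only, and that all adverse events of eliminated cases stay in the safety summaries.
- Reconcile the elimination, withdrawal and analysis-dataset sections: say which applies to prohibited medication and inadequate exposure, and what the full dataset in the withdrawal section means.

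The cost is a few sentences and no new data. The downside is a denominator that includes some participants with little safety follow-up. Reporting the number without any scheduled evaluation, with their last contact, makes that visible.

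The same definition also requires a dose of the pill, which leaves the control group outside the safety set. That is a separate point, and deleting the evaluation condition does not resolve it, so both should be handled in the same edit.
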